### Experimental Conditions

This study will compare the subjective reports of children, caregivers, and healthcare providers who participate in a randomized crossover trial of VR versus standard of care (control). In the standard of care treatment condition, participants will receive the standard CHLA treatment protocol for the medical procedure. The intervention group will receive standard CHLA treatment with VR distraction.

Children and their caregivers will be informed that they will be randomized to either the VR or standard of care condition. They will be told about both conditions and informed that if they are assigned to the control condition, patients will be able to play with the VR after the medical procedures and study measures are completed. Children will be told that they cannot decide on their treatment condition. Children in the VR condition will undergo the invasive procedure while distracted by interaction with an immersive virtual environment (VE) presented via a head mounted display (HMD).

### Virtual Reality Technology

Four types of VR HMDs are available for use in this study. Participants 13 -21 years old can use the Samsung Gear VR. Participants 10-21 years can use the Merge, Oculus Go, and Mira Prism. The VE to be used in this study is mobile based and has active matrix LCDs with high pixel resolution, creating a bright, vibrant color and a quality image. This VE has already been utilized in lab studies with children without any reported or observed difficulties.

Within the VE, users can watch age-appropriate movies (up to parent's discretion) or engage in BearBlast (developed by Applied VR). The movie-watching VE places the user in a virtual movie theater environment, complete with velvet red seats. No movement is required and the user only has to look at the large movie screen ahead to watch the movie. In BearBlast, users travel on a pre-set path through a colorful, vibrant, highly interactive environment, filled with toy-like trees, mountains, rainbows, mushrooms, and bushes. As they gaze, they control the direction of a continuously firing cannon, which interacts with items in the world and positively reinforces experimentation and activity. They automatically enter a new level every 2.5 minutes, keeping the environment continuously fresh. Throughout the world, plush moles play the role of antagonist, standing in for the nuisance and distraction of pain. The VR game is equipped with a head-tracking system, enabling the player to look around the virtual environment. In addition, there is the option to interact with the VR environment using a tap pad located on the side of the helmet. Therefore, the child will be receiving distraction via 3-D visual and auditory sensory, and tactile feedback, thus supplying a multi-sensory immersive experience. While wearing these glasses, the children only can see the HMD screen so that the immersion and presence will be increased. The VR glasses will be sanitized before and after every use so that the chance of infection will be minimized.

The Mira Prism is a portable, augmented reality (AR) HMD powered by iPhone. When paired with the iPhone, the Mira Prism goggles can superimpose computer-generated images on the user's view of the real world. Unlike the full immersion of VR, AR allows users to view the outside world while interacting with digital content. In this study, the patient can interact with Magic Mallet (developed by Miney Moe). Magic Mallet is a distraction game designed for pain management and communication during procedures. The game automatically adjusts cognitive load for optimal effect for users. Study team iPhones specifically loaded with Magic Mallet, and without cellular capability, will be used with the Mira Prism.

We will ensure that the Mira Prism is not used with patients who have symptoms of "squint, amblyopia, or anisometropia" through our eligibility screening of all patients, performed prior to the informed consent process. One of the exclusion criteria in our study is "Children with visual, auditory, or tactile deficits that would interfere with the ability to complete the experimental tasks or use the technological devices." We will not enroll children with any visual deficits.

The manuals for Oculus Go and Mira Prism both state that these devices should not be used by children under 13 years of age because the headset is not sized for children and improper sizing can lead to discomfort. This warning has to do with hardware design rather than actual safety. Both devices have been used across the country by children under 13 years of age. We will always tighten the adjustable straps of these devices to ensure that they are comfortable for children under 13 years.

### Patient Procedures and Data Collection

After informed consent and assent have been obtained and the patient has successfully met the screening criteria for cognitive ability, the patient and his/her caregiver will be enrolled into the study. Patients and their caregivers will be asked to fill out several questionnaires via Qualtrics on an individual IPAD (see uploaded Table of Measures) in the private area/room.

In order to ensure that pre-existing pain or anxiety do not contaminate reports of procedural pain or virtual reality-related symptomatology, the patient will be asked to report pre-procedure baseline levels for the following measures: the Visual Analog Scale (VAS), the Faces Pain Scale Revised (FPS-R), the Colored Analogue Scale (CAS) for pain, the VAS for procedural anxiety, the Facial Affective Scale (FAS), the Childhood Anxiety Sensitivity Index (CASI), and the Malaise Scale. If patient is age 18 or above, they will also complete a demographic form. This is expected to take approximately 15 minutes.

After patients have completed the pre-procedural battery on the IPAD, and patients and caregivers will be informed about their assigned study condition (VR or standard of care). Children in the VR distraction groups will then begin interacting with the virtual environment for approximately 5 minutes. Following the 5-minute VR primer period the procedure will commence. Following the procedure, children will continue to play the VR game for approximately 2 minutes. Children in the standard care control group will undergo the medical procedure according to the existing CHLA protocol. Regardless of treatment condition, the Research Assistant will observe and record the behavior of the child while s/he is undergoing the medical procedure. A video tape recording of the procedure will also be obtained (if the child, caregiver, and healthcare provider have agreed to be recorded) in order to later score the behavior of the child according to the Child-Adult Medical Procedure Interaction Scale – Revised (CAMPIS-R). Video will be focused on the patient/caregiver and not on the healthcare provider. However, it is possible that the healthcare provider's voice or appendage will be recorded while interacting with the patient and therefore their verbal consent will be obtained as well. Video recording will later be coded for signs and symptoms of anxiety and behavioral distress in the patient and his/her caregiver.

Following completion of the medical procedure, all children will complete the VAS and CAS to report pain intensity, the FPS-R, the VAS and FAS for procedural anxiety, the Malaise Scale, the Child Presence Questionnaire (VR group only), and the Satisfaction Questionnaire via Qualtrics on the IPAD. This is expected to require approximately 15 minutes.

Following completion of these measures, children who were not randomized to the VR condition will have the opportunity to use the VR.

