#### Study Team Procedures and Data Collection

The PI, Co-I, or research assistant will complete the case report form on the IPAD (before the child completes the post-measures). They will also complete observational measures (i.e., the CAMPIS-R) to record the patient's distress, modes of coping prior to the procedure, and other observational data during the medical procedure. With the consent of participants, all procedures will be videotaped, to allow a member of the study team to review the tape for more accurate behavioral observations. The video camera will focus on the patient's behavioral distress and reactions prior to and during the medical procedure. Video recording will focus on the participants rather than on the medical procedure. Video tapes will later be rated and coded based on the Child-Adult Medical Procedure Interaction Scale - Revised (CAMPIS-R) by two independent raters. An examination of inter-rater reliability (Kappa statistic) will be employed to evaluate the reliability between the coders and a accurate measure of the observational behavioral distress ratings.

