### 12.2. Describe the statistical considerations for the study, how the sample size was determined, and how the results will be analyzed, if applicable. *(Refer to specific sections of the protocol/grant, if applicable)*

Power analyses based on preliminary data from the PI's previous VR and phlebotomy study determined that 100 participants are needed for the current study. The power calculation is based on the pain intensity VAS, which is calculated as a continuous (0 to 100) variable. 120 patients will be recruited for each type of painful medical procedure to account for attrition/drop out. In other words, 120 patients receiving venipuncture will be recruited, and a separate 120 patients receiving IV placement will be recruited. A total sample size of 100 patients per medical procedure type would result in 25 patients in each of the 4 age-gender strata groups. In our earlier preliminary data the VR pain score was about half that of the other methods giving an effect size of about 1.5. This would result in 80% power for a 2-sided t-test at the .05 significance level. Because we have several covariates planned in this study, we will increase the required sample size by (at least) 20% to allow for adjustment of the covariates. A general rule of thumb is to increase the sample size by 10-20% for each major covariate. Therefore, the proposed sample size of 240 (120 per procedure), assuming some attrition/drop-out will result in more children in each group.

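### The time from the end of the procedure to the child's pain and anxiety ratings is not matched by arm: VR children play for about 2 more minutes first, and controls have no stated interval

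*Protocol*

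**What the plan says.** The sequence has to be put together from several parts of Protocol section 12.1.

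- **VR arm** (Patient Procedures and Data Collection): a primer of about 5 minutes, the procedure, and then "Following the procedure, children will continue to play the VR game for approximately 2 minutes".
- **Control arm** (same section): "Children in the standard care control group will undergo the medical procedure according to the existing CHLA protocol". No step is described between the end of the procedure and the ratings.
- **Child ratings, both arms** (same section): "Following completion of the medical procedure, all children will complete the VAS and CAS to report pain intensity", together with the FPS-R and the anxiety VAS and FAS, all on the iPad. No time or window is given.
- **Control access to VR** (same section): "Following completion of these measures, children who were not randomized to the VR condition will have the opportunity to use the VR". It comes after the ratings, so it supplies no matching interval before them.
- **Headset** (Virtual Reality Technology): "While wearing these glasses, the children only can see the HMD screen". The Mira Prism, an augmented-reality device, is the exception, since it leaves the surroundings visible.
- **Staff step** (Study Team Procedures and Data Collection): a team member "will complete the case report form on the IPAD (before the child completes the post-measures". No duration is given, and no difference by arm.

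Section 12.2 makes the child's pain rating the sizing outcome: "The power calculation is based on the pain intensity VAS, which is calculated as a continuous (0 to 100) variable".

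**The concern.** The comparison of arms should differ only in the treatment. Here the plan, followed literally, also makes the arms differ in how long after the needle the child is asked to rate it. Pain and fear from a brief procedure may ease over minutes. If they do, and VR children are asked later, part of the difference in scores reflects when the question was put and not what VR did during the procedure.

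The outcomes exposed are the child's own post-procedure ratings of pain and anxiety, which are central to Hypothesis 1 and include the VAS used for the sample size. Because the delay goes with the arm, the planned adjustment for baseline scores and covariates would not separate it from the treatment effect. The protocol takes baseline ratings so that pain or anxiety already present does not distort the procedural reports. It has no comparable protection for the timing of the ratings afterwards.

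**Working it through.** The point concerns the order of events and does not rest on a figure in the plan, so the main check is a side-by-side reading.

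**Step 1. Planned gap from end of procedure to first child rating.**

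| | VR arm | Control arm |
|---|---|---|
| Stated activity after the procedure | about 2 minutes of play | none stated |
| Case report form before ratings | yes, duration not stated | yes, duration not stated |
| Fixed rating time | none | none |

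**Step 2. Can VR children rate during the play?** With the immersive headsets they cannot see the iPad, so the ratings must wait. With the Mira Prism they could in principle, though the order of the text still puts play first. The protocol does not state outright that play ends before rating; this is an inference from the order of the text and the headset description.

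**Step 3. Net difference.** Let *c* be the time for the case report form and ignore handling.

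- Form completed after the play: VR gap = 2 + *c*, control gap = *c*, difference = 2 minutes.
- Form completed during the play: VR gap = the larger of 2 and *c*, control gap = *c*. The difference is 2 − *c* if *c* is under 2 minutes, and 0 otherwise.

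The planned difference therefore lies between 0 and about 2 minutes, depending on a choice the protocol leaves open.

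**Step 4. What a shift would do (assumed range).** The documents give neither a rate of fading nor an SD for the VAS. Suppose VR has no true effect and later rating alone lowers VR scores by *d* SD. For a two-sided t-test at 0.05 with *n* per arm, the non-centrality is *d* × √(*n*/2). Section 12.2 gives 100 needed and 120 recruited per procedure type, so *n* is 50 or 60 with equal allocation.

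| Assumed shift *d* | Non-centrality, *n* = 50 | Rejection rate, *n* = 50 | Non-centrality, *n* = 60 | Rejection rate, *n* = 60 |
|---|---|---|---|---|
| 0 | 0 | 5% | 0 | 5% |
| 0.1 | 0.1 × 5 = 0.50 | 8% | 0.1 × 5.48 = 0.55 | 8% |
| 0.2 | 0.2 × 5 = 1.00 | 17% | 0.2 × 5.48 = 1.10 | 19% |
| 0.3 | 0.3 × 5 = 1.50 | 32% | 0.3 × 5.48 = 1.64 | 37% |

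**Step 5. The same shifts against the planned effect.** Section 12.2 describes preliminary data "giving an effect size of about 1.5". The assumed shifts are 0.1/1.5 = 7%, 0.2/1.5 = 13% and 0.3/1.5 = 20% of that. If the true effect is that large, such a shift would not change the conclusion and would only inflate the estimate. It matters more if the true effect is small.

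Steps 4 and 5 show sensitivity only. They do not estimate the bias.

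**The case against.** Five points can be made for the plan.

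1. **The case report form may close the gap.** It precedes every child's ratings, and if staff complete it while VR children play, the difference shrinks or vanishes (Step 3). This stands as a possibility. The protocol does not require that order, so the arms are not matched by design.

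2. **Children may be rating the procedure as recalled.** The protocol speaks of procedural pain and procedural anxiety, and the item wording may be in the Table of Measures, which is not shown. A short lag would then matter less. This stands: one cannot say that the recall period is missing, only that it should be confirmed.

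3. **Post-procedure play is part of the intervention.** Any effect of a pleasant activity just before rating can be read as part of the VR package. This also stands. Matching the clock removes the difference in elapsed time and not the difference in activity, and it need not do more.

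4. **Caregivers.** A reader might infer that caregiver ratings carry the same timing difference. The documents do not support that. Under Caregiver Procedures and Data Collection, caregivers use their own iPad, are not tied to the child's play, and are already asked about pain while the procedure took place.

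5. **Behavioural distress.** It is observed before and during the procedure, so that part of Hypothesis 1 is not affected by the time of rating.

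**Conclusion.** The point holds in a limited form. As written, the plan gives VR children about 2 more minutes before they can rate, sets no matching interval for controls, and fixes no rating time in either arm. VR children will therefore tend to rate later, by up to about 2 minutes, unless the case report form happens to take up the difference.

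A reader might go further and conclude that the bias certainly favours VR, or put a figure on it. The documents support neither. If pain or anxiety fades over the interval, the shift would favour VR, but no fading rate is given, and recall of the procedure may hardly change in that time. The effect may be small. The conclusion rests on two assumptions: that play comes before rating, which is firm for the immersive headsets and weaker for the Mira Prism, and that staff do not routinely complete the form during the play.

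This does not invalidate the trial. It is a foreseeable and avoidable difference on the outcome the trial is sized on, and worth correcting because doing so is nearly free.

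**What to change.** In section 12.1, Patient Procedures and Data Collection:

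- State one elapsed time from the end of the procedure to the start of the child's questionnaire for both arms, about 2 minutes, with the case report form completed in that window.
- Record the end of the procedure and the questionnaire start time on the iPad, so that the match can be checked by arm.
- Confirm that the child's pain and anxiety items ask about the procedure itself, as the caregiver pain item already does, and reword them in both arms if they do not.

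The cost is about 2 minutes of waiting per control child, some of it used by a form that has to be completed anyway, plus two time entries. With 60 controls per procedure type this is 60 × 2 = 120 minutes over the whole recruitment for that procedure. No measures or staff are added. Post-procedure play stays as part of the VR package being compared.

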#### Caregiver Procedures and Data Collection

After informed caregiver consent and child assent is obtained the caregiver will complete a brief demographic survey and baseline VAS, FPS-R, CAS, and FAS estimates of their child's pre-procedural pain and anxiety via Qualtrics on an individual IPAD. This will require approximately 10 minutes. Note that the caregiver may not participate if the patient is age 18 or above.

Following the medical procedure, caregivers of all children age 10-18 will complete VAS, FPS-R, and CAS measures to estimate their perception of their child's pain during the medical procedure and VAS and FAS measures of procedural anxiety. Parents will also complete a Satisfaction Questionnaire. These questionnaires will again be presented via Qualtrics on an individual IPAD. This will require approximately 10 minutes.

#### Healthcare Providers' Responsibilities and Involvement:

Healthcare providers will be asked to continue with their standard duties and to complete a VAS and CAS measure of their perceptions of the child's pain and anxiety via a healthcare provider survey (satisfaction questionnaire). Because the questionnaire is not part of their routine duties, they will be provided with an information form detailing the study procedures. Following completion of the medical procedure, the healthcare provider will complete a 7-item measure about their perception of the patient's cooperation and distress as well as their satisfaction with the procedure. Completion of this measure is expected to require approximately 5 minutes or less. If the healthcare provider does not wish to participate, the patient may still participate in the study, but will not be videotaped. The healthcare provider will not be asked to complete the questionnaire.

#### Study Team Procedures and Data Collection

The PI, Co-I, or research assistant will complete the case report form on the IPAD (before the child completes the post-measures). They will also complete observational measures (i.e., the CAMPIS-R) to record the patient's distress, modes of coping prior to the procedure, and other observational data during the medical procedure. With the consent of participants, all procedures will be videotaped, to allow a member of the study team to review the tape for more accurate behavioral observations. The video camera will focus on the patient's behavioral distress and reactions prior to and during the medical procedure. Video recording will focus on the participants rather than on the medical procedure. Video tapes will later be rated and coded based on the Child-Adult Medical Procedure Interaction Scale - Revised (CAMPIS-R) by two independent raters. An examination of inter-rater reliability (Kappa statistic) will be employed to evaluate the reliability between the coders and a accurate measure of the observational behavioral distress ratings.

#### Non-Randomization Protocol

There is a second version of the current protocol that does not include randomization for patients undergoing select painful procedures. In this version, all study subjects will use a virtual reality headset during the duration of the procedure. All participants will answer questions regarding the efficacy of VR similar to those answered by the experimental group participants in the original version of the current protocol.

### 12.2. Describe the statistical considerations for the study, how the sample size was determined, and how the results will be analyzed, if applicable. *(Refer to specific sections of the protocol/grant, if applicable)*

Power analyses based on preliminary data from the PI's previous VR and phlebotomy study determined that 100 participants are needed for the current study. The power calculation is based on the pain intensity VAS, which is calculated as a continuous (0 to 100) variable. 120 patients will be recruited for each type of painful medical procedure to account for attrition/drop out. In other words, 120 patients receiving venipuncture will be recruited, and a separate 120 patients receiving IV placement will be recruited. A total sample size of 100 patients per medical procedure type would result in 25 patients in each of the 4 age-gender strata groups. In our earlier preliminary data the VR pain score was about half that of the other methods giving an effect size of about 1.5. This would result in 80% power for a 2-sided t-test at the .05 significance level. Because we have several covariates planned in this study, we will increase the required sample size by (at least) 20% to allow for adjustment of the covariates. A general rule of thumb is to increase the sample size by 10-20% for each major covariate. Therefore, the proposed sample size of 240 (120 per procedure), assuming some attrition/drop-out will result in more children in each group.

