#### Statistical Analysis

All data collected will be entered, coded, scored and analyzed using SPSS 22.0. Descriptive analyses will be performed to report demographics and to examine all means/standard deviations/correlations amongst the variables of interest. Once the integrity of the data is validated the following analyses will be conducted.

Aim 1. To determine if VR is more effective than standard care for reducing pain and anxiety in children undergoing painful medical procedures.

Hypothesis 1: Patients in the VR condition will report significantly less pain, anxiety, and distress (i.e., measured via self-report, parent-report, and behavioral observations compared to standard of care for patients undergoing a painful medical procedure.

For this hypothesis, there are 6 child outcome areas that will be evaluated: pain intensity, affective pain, child anxiety, anticipatory anxiety, and behavioral distress. When applicable, differences controlling for baseline variables, as well as differences in post measures will be evaluated. A univariate analysis will be performed to assess for differences in baseline variables between the two groups (VR versus standard of care). In addition the influence of any possible covariates such as child age, gender, or other demographic variables (e.g., previous experience with that medical procedure) might have on the six principal outcome measures will be investigated through a multivariate correlation analysis. If covariates are found to significantly relate to outcomes, they will be included in the multivariate analyses.

Aim 2. To evaluate caregiver's assessment patient distress and satisfaction with VR compared to standard of care for patients undergoing painful medical procedures.

Hypothesis 2: Caregivers will perceive less pain/anxiety in their children and greater have satisfaction during the VR condition compared to standard of care for patients undergoing painful medical procedures.

For this hypothesis, caregiver report of child pain, caregiver report of child anxiety, and caregiver satisfaction will be compared between the VR and the standard of care groups using a univariate analysis. The independent variable will be treatment type (standard of care/VR), and the dependent variables will be caregiver perception of child pain/anxiety, and caregiver satisfaction.

Aim 3: To evaluate healthcare provider's assessment of patient cooperation and their satisfaction with VR compared to standard of care.

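### Venipuncture and IV placement are sized as two separate cohorts, but each aim states one VR v standard of care comparison with no procedure term; the analysis should be matched to the sizing

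*Protocol*

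**What the plan says.** **Sizing (Protocol 12.2).** The power analysis "determined that 100 participants are needed for the current study". The figure is then applied to each procedure type: "120 patients receiving venipuncture will be recruited, and a separate 120 patients receiving IV placement will be recruited", making 240 in all. The evaluable number is also given per procedure: "A total sample size of 100 patients per medical procedure type would result in 25 patients in each of the 4 age-gender strata groups". The power statement reads "This would result in 80% power for a 2-sided t-test at the .05 significance level", and the outcome behind it is named: "The power calculation is based on the pain intensity VAS, which is calculated as a continuous (0 to 100) variable".

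**Analysis (Protocol 12.2, Statistical Analysis).** Aim 1 is "To determine if VR is more effective than standard care for reducing pain and anxiety in children undergoing painful medical procedures". Its hypothesis is one contrast between VR and standard of care. Neither venipuncture nor IV placement is named. The example covariates are age, gender and other demographic variables, such as earlier experience of the procedure; procedure type is not among them. For Aims 2 and 3, treatment type is the only independent variable.

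**Randomization (Protocol 12.1, Stratified Randomization Design).** The list is divided by gender. The opening of 12.1 also speaks of balancing age. Procedure type appears in neither place.

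**The concern.** The sizing text treats the study as two trials under one protocol, while the analysis text is worded as one. The reader cannot tell whether Aim 1 is answered once, in all patients, or twice, once per procedure. Each reading has its own cost.

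- **One comparison across all patients.** The procedure-specific questions that fixed the sample size get no stated answer. With no procedure term, and no stratification by procedure, any difference in pain between the two procedures, together with chance imbalance of procedures between arms, stays in the error term.
- **One comparison per procedure.** Two tests at the full .05 would stand behind an aim worded for painful procedures in general, and the text does not say how two results bear on that one aim.

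**Working it through.** **Inputs.** From Protocol 12.2: two-sided alpha .05; power 80%; effect size about 1.5 ("the VR pain score was about half that of the other methods giving an effect size of about 1.5"); 100 evaluable and 120 recruited per procedure; 240 in total. From 12.1: balanced allocation, taken here as 50 per arm per procedure. Assumed, because the documents give no figure: mean pain differs between the two procedures by D = 0.3, 0.5 or 0.8 SD, and the two procedures contribute equal numbers.

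**1. The plan's own figures.** The step to the recruited number reproduces: 100 × 1.2 = 120, and 2 × 120 = 240. So 12.2 does build the total from two separately sized cohorts. The 100 does not follow from an effect size of 1.5. A two-sample t-test at two-sided .05 has power 0.797 with 8 per arm and 0.848 with 9 per arm, so 9 per arm (18 in total) suffices. With 50 per arm, power at d = 1.5 exceeds 99.99%, and 80% power corresponds to d of about 0.57. This is a separate sizing problem and the present point does not rest on it.

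**2. The two readings answer different questions.** At 80% power, 50 per arm (one procedure) detects d of about 0.57; 100 per arm (both procedures, evaluable) detects d of about 0.40. Section 12.2 sizes only the first.

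**3. Cost of a pooled analysis without a procedure term.** With half the patients at +D/2 and half at −D/2 around the common mean, and within-procedure SD 1, the between-procedure variance is D²/4. Variance inflation is therefore 1 + D²/4.

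| Assumed D (SD) | Inflation | Equivalent of 200 evaluable patients |
|---|---|---|
| 0.3 | 1 + 0.09/4 = 1.0225 (2%) | 200/1.0225 ≈ 196 |
| 0.5 | 1 + 0.25/4 = 1.0625 (6%) | 200/1.0625 ≈ 188 |
| 0.8 | 1 + 0.64/4 = 1.16 (16%) | 200/1.16 ≈ 172 |

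A fixed procedure factor removes this variance and adjusts for chance imbalance of procedures between arms.

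**4. False-positive rate under the per-procedure reading.** The cohorts are disjoint, so under the null their tests are independent. For one outcome:

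- either cohort alone supports one general claim: 1 − (1 − 0.05)² = 0.0975;
- the same, counting only results in favour of VR: 1 − (1 − 0.025)² = 0.0494, against 0.025;
- two claims, each confined to its own procedure: 0.05 each;
- one pooled test: 0.05.

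**The case against.** **The passages can be read together.** Hypotheses 1 and 3 speak of a procedure in the singular, and the covariate example refers to experience with that same procedure. An analysis template applied once to each cohort fits this wording, and two groups are compared within either cohort. The phrase "assess for differences in baseline variables between the two groups (VR versus standard of care" describes a baseline-balance check and does not show that outcomes are to be pooled. All of this stands: the text never says that the cohorts are pooled. Equally, no sentence says that they are analysed apart, and Aims 1 and 2 use the plural.

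**A statistical analysis plan may settle it.** Model terms and alpha allocation are properly left to such a plan, and their absence here is not the point. The point is that sizing and analysis, both within section 12.2, do not fit as written.

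**Procedure could enter as a covariate.** The covariate list is open, and variables related to outcome are to be included. A large procedure effect might therefore be picked up, but only if procedure type is screened and passes. Naming it in advance is simpler.

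**Stronger readings.** A reader might infer that the Aim 1 error rate is doubled, or reaches 11.5% (by simulation) if the pooled test may also decide. The documents do not support that, because nowhere do they say that a positive result in either cohort, or in the pool, suffices. A reader might also infer that the cohorts will often disagree. That holds only at effect sizes well below the one stated; at about 1.5, both cohorts would almost certainly be significant. Finally, a reader might infer that a pooled test must gate the cohort tests. That is one trade-off among several: it puts a contrast that was not sized ahead of two that were.

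**Conclusion.** The mismatch is real but limited. Section 12.2 sizes two procedure cohorts, while the aims state one treatment comparison with no procedure term and the randomization does not stratify by procedure.

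The certain consequence is that the stated analysis does not say whether it answers the per-procedure questions that set the sample size. If it is run pooled without a procedure term, precision is lost to the extent of 2% to 16% extra variance. That range rests on assumed procedure differences of 0.3 to 0.8 SD and equal cohort sizes. The 9.75% false-positive rate applies only if a general claim were allowed to rest on either cohort alone, and it is for a single outcome. It is a risk to close off, not a demonstrated property of the plan.

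The point does not stop the trial, but it should be corrected because the correction is nearly free.

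**What to change.** Make the Aim 1 analysis in Protocol 12.2 match the sizing by adopting one of two forms.

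- **(a) Two procedure-specific questions.** State one hypothesis and one two-sided .05 test for venipuncture, and the same for IV placement. Limit each claim to its own procedure. This follows the existing sizing most closely.
- **(b) One general question.** Use a single two-sided .05 test of VR v standard of care in all randomized patients, with procedure type as a fixed factor. Report the within-procedure estimates and the treatment-by-procedure interaction with 95% confidence intervals as supportive. Use the same procedure term in the models for Aims 2 and 3.

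The cost is one or two sentences and, under (b), one model term, with no extra patients or data. The price of (a) is that neither result alone supports a claim about painful procedures in general. The price of (b) is that the within-procedure results are supportive only.
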